## 1. List of abbreviations

COVID-19... Corona Virus Disease 2019

CNI... Calcineurin inhibitor

CRF... Case Report Form

EMA... European Medicines Agency

GCP... Good Clinical Practice

i.m. ... intramuscular

mRNA... messenger Ribonucleic Acid

SAE... Serious Adverse Event

SARS-CoV-2... Severe Acute Respiratory Syndrome Coronavirus type 2

SUSAR... Suspected Unexpected Serious Adverse Reaction

| Visits                         | Number | 1                                   | 2         | 3                                   | 4                                   | 5                                    | 6                                      | 7                                      |
|                                | Name   | Screening                           | Treatment | Follow up 1                         | Follow up 2                         | Follow up 3                          | Follow up 4                            | Follow up 5                            |
|                                | Time   | within 28 days prior to vaccination | Day 1     | Day 29-42 (4 weeks after treatment) | Day 57-70 (8 weeks after treatment) | Day 85-98 (12 weeks after treatment) | Day 168-196 (24 weeks after treatment) | Day 336-364 (48 weeks after treatment) |
| Informed consent               |        | x                                   |           |                                     |                                     |                                      |                                        |                                        |
| Inclusion / Exclusion Criteria |        | x                                   |           |                                     |                                     |                                      |                                        |                                        |
| Medical History                |        | x                                   |           |                                     |                                     |                                      |                                        |                                        |
| Concomitant medication         |        | x                                   |           |                                     |                                     |                                      |                                        |                                        |
| SARS-CoV-2 Antibodies          |        | x                                   |           | x                                   | x                                   | x                                    | x                                      | x                                      |
| T-cell response                |        | x                                   |           | x                                   |                                     |                                      |                                        |                                        |
| Pregnancy test                 |        | x                                   | x         |                                     |                                     |                                      |                                        |                                        |
| Adverse events                 |        |                                     | x         | x                                   | x                                   | x                                    | x                                      | x                                      |

**Table 1:** Visit and Assessment scheduled

### 3. Background

Kidney transplant recipients are at high risk for a severe COVID-19 disease course and therefore prioritized to receive early vaccination against SARS-CoV-2 (1, 2). In general, the immune response to vaccination is reduced in immunosuppressed individuals including kidney transplant recipients. A recent study from Israel confirmed that only 37.5% of kidney transplant recipients developed detectable antibodies against the spike protein following full vaccination with BNT162b2 (Pfizer-BioNTech) (3). The type of maintenance immunosuppression may have a significant impact on the immune response in kidney transplant recipients. Patients treated with co-stimulation blockade (Belatacept) as maintenance immunosuppression showed even lower immunization rates of only 5.7 % (4).

Several strategies have been proposed to improve response to SARS-CoV-2 vaccination including additional dosing and mixing different vaccine types to broaden the presented antigen repertoire (heterologous vaccination or “mix-and-match strategy”) (5). Recent data show a higher reactogenicity of heterologous boosting in the general population (6). In the European Union there are currently two different classes of SARS-CoV-2 vaccines available: a) mRNA (mRNA-1273 [Moderna Biotech] and BNT162b2 [Pfizer-BioNTech]) and b) viral vector-based vaccines (ChAdOx1 [AstraZeneca] and Ad26COVS1 [Jansen]). Of these Ad26COVS1 is the only vaccine that has been shown to induce a protective immune response after a single dose (7). Kidney transplant recipients in Austria have primarily been vaccinated with mRNA-based vaccines.

## Study rationale

More than half of all kidney transplant recipients do not develop SARS-CoV-2 antibodies following full vaccination with a mRNA-based SARS-CoV-2 vaccine. However, there is currently no data available to guide immunization strategies in these patients. A “mix and match” strategy combining different types of vaccines has been proposed to improve immune response following vaccination, but efficacy of such a strategy in kidney transplant recipients has not yet been evaluated.

## 4. Study objective:

The primary objective of this study is to test if a “mix and match” strategy (using a viral vector-based vaccine) results in a better antibody response against the SARS-CoV-2 spike protein compared to an additional dose of mRNA vaccine (“more-of-the-same”) in patients who did not develop antibodies following full vaccination with a mRNA vaccine.

## Primary objective (Hypotehsis)

We specifically hypothesize that a single dose of the viral vector-based vaccine Ad26COVS1 [Jansen] results in a higher rate of antibody response compared to a third dose of the previously used mRNA vaccine (mRNA-1273 [Moderna Biotech] or BNT162b2 [Pfizer-BioNTech]).

## Primary Endpoint

- Number of patients presenting a positive humoral immune response (antibody), assessed with the Roche ELISA test using the manufacturer recommended cutoff of

0.8U/ml, to the SARS-CoV-2 vaccine at 4 weeks after the vaccination. The decision to perform a responder analysis is motivated by the fact that currently the exact relationship between anti-SARS-CoV-2 antibody concentration and protective immunity is not known.

### Secondary endpoints

- Number of patients presenting a positive humoral immune response (antibody), assessed with the Roche ELISA test using the manufacturer recommended cutoff of 0.8U/ml, to the SARS-CoV-2 vaccine at 8, 12, 24, 48 weeks after the vaccination.
- Number of detectable antibodies (U/ml measured by the Roche ELISA test) at 4, 8, 12, 24 and 48 weeks after vaccination.
- Number of patients presenting a positive cellular immune response defined as doubling of extracellular IFN $\gamma$  concentration in the plasma after ex-vivo re-stimulation with a SARS-CoV-2 spike protein peptide pool at 4 weeks after the vaccination.
- Strength of the cellular response to SARS-CoV-2 spike protein peptides measured in terms of the extracellular IFN $\gamma$  concentration after ex-vivo re-stimulation with a peptide pool at 4 weeks after the vaccination.
- incidence of COVID-19 disease within 24 and 48 months after vaccination

## 5. Study design

This is a single center, single blinded, randomized study. Only the patient will be blinded for the type of vaccine administered. Based on sample-size calculations (see below) a total of 200 patients will be enrolled into the study.

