### Blinding

Patients will be blinded for the treatment.

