## Treatment

Patients will receive a single dose of the study drug intra muscular (i.m.) within 28 days after screening. Patients will receive a time slot for vaccination following randomization.

Vaccination will be performed at the outpatient clinic of the Division of Nephrology and Dialysis at the Medical University of Vienna (chronic hemodialysis unit and pre-transplant clinic).

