### Laboratory testing

- SARS-CoV-2 spike protein and nucleocapsid antibodies at Visit 1, Visit 3, Visit 4, Visit 5, Visit 6 and Visit 7 (9ml blood)
- SARS-CoV-2 specific T- cell response at Visit 1 and Visit 3 (3x8 ml blood)

Antibodies will be measured by the Department of Laboratory Medicine using clinically validated ELISA tests (Roche, Switzerland). SARS-CoV-2 specific T-cell responses will be assessed by QuantiFERON assays with SARS-CoV-2 specific peptides at the research laboratory of the Division of Nephrology (Quiagen, Netherlands).

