Before carrying out any endpoint analysis the number of study participants either on co-stimulation blockade or CNl as well as the number of patients who were initially vaccinated with either mRNA-1273 or BNT162b2 will be determined. In case of sufficient number of study subjects with different immunosuppressants or initially received vaccines the statistically analysis plan will be updated to introduce additional stratification.

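### Blinding stops at the patient: nothing keeps the allocation from the T-cell laboratory or from those who settle the per-protocol set and the stratification

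*Protocol*

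**What the plan says.** Section 5 (Study design) describes the trial: "This is a single center, single blinded, randomized study". The next sentence sets the extent of the blinding: "Only the patient will be blinded for the type of vaccine administered". The Blinding subsection of section 6 adds only this: "Patients will be blinded for the treatment".

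The two laboratories are named under Laboratory testing in section 6. For the antibody endpoints, including the primary one: "Antibodies will be measured by the Department of Laboratory Medicine using clinically validated ELISA tests". For the cellular endpoints: "SARS-CoV-2 specific T-cell responses will be assessed by QuantiFERON assays with SARS-CoV-2 specific peptides at the research laboratory of the Division of Nephrology". The Treatment subsection gives the place of vaccination: "Vaccination will be performed at the outpatient clinic of the Division of Nephrology and Dialysis at the Medical University of Vienna".

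Section 8 makes the analysis of every endpoint per protocol. Its closing paragraph calls for counts of patients by immunosuppressant and by initial mRNA vaccine before any endpoint analysis. If the numbers are sufficient, "the statistically analysis plan will be updated to introduce additional stratification".

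Two provisions already help. Subject enrollment (section 6) requires the subject identification number on all study documentation, and Safekeeping (section 9) provides for a pseudonymised database.

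**The concern.** The word *only* in section 5 makes this a stated design choice rather than a detail left to the analysis plan. An analysis plan that masked the laboratory or the statistician would sit awkwardly with it.

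Two kinds of exposure follow.

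- **Measurement.** The week-4 IFN-gamma results come from a laboratory in the division that gives the vaccine and therefore knows the arm. The protocol puts no barrier between the two.
- **Decisions.** Someone must decide which patients count as per protocol, and whether the analysis is to be stratified further. The protocol lets people who know the arm, and who may have seen individual week-4 results, take both decisions. The first of them bears on the primary comparison, however objective the assay.

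At stake is mainly how well the result withstands challenge. A reader of the final report could ask whether exclusions or the choice of analysis were made with the arms in view, and the protocol as written offers no answer.

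**Working it through.** **1. Design figures, and whether masking alters them.** Inputs from Sample size calculation (section 8): response 30% and 50%, alpha 5%, power 80%, dropout at most 5%, 100 per group. The sidedness of the test is not stated; two-sided is assumed.

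- The pooled rate is (0.30 + 0.50)/2 = 0.40.
- n per arm = [1.96 × √(2 × 0.40 × 0.60) + 0.842 × √(0.30 × 0.70 + 0.50 × 0.50)]² / 0.20² = (1.358 + 0.571)² / 0.04 ≈ 93.
- With dropout: 93 / 0.95 = 97.9, so 98 per arm, against 100 planned.
- Power at 95 evaluable per arm (100 × 0.95): z = (0.20 × √95 − 1.358) / 0.678 = 0.87, which gives 80.8%. At 100 per arm it is 82.8%.

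The protocol's figure reproduces. Who is masked enters none of these inputs, so the fix changes neither sample size nor power.

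**2. Where knowledge of the arm could act.** The table sets the relevant provisions side by side.

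| Step | What the protocol fixes | What it leaves open |
|---|---|---|
| Primary antibody result | Separate department, validated ELISA, cutoff 0.8 U/ml | Very little; it does not say that samples arrive without allocation |
| Cellular response (two of the five listed secondary endpoints) | Numerical rule: doubling of IFN-gamma against the patient's own negative control; declared exploratory | Laboratory in the vaccinating division; no statement that samples arrive without allocation |
| Per-protocol set | Used for all endpoints | No statement that membership is settled without knowledge of the arm; some withdrawals rest on the investigator's judgement (Withdrawal of subject, section 6) |
| Added stratification | Counts of two baseline factors, taken before any endpoint analysis | The threshold for a sufficient number, and whether the decision is taken masked |

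**3. Reading the table.** The first row leaves almost no room for bias. In the second, the responder rule is arithmetic, so knowledge of the arm could act only on the concentrations that go into it, for instance through a decision that a control or a run is invalid. The protocol describes no such step, so this is a possible route and not a documented one. The third row matters most for the primary result, because a set chosen with the arms known can shift an objective comparison. The fourth has a partial safeguard: the counts concern baseline factors and come before endpoint analysis. That timing does not stop individual week-4 results from being known to the people who decide.

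**4. Means already in place.** The subject number and the pseudonymised database provide the coding. What is missing is a sentence saying that the allocation does not travel with the code.

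**The case against.** The case for leaving the text alone has real strength.

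- *The sentence merely explains the term single blinded.* That is a fair reading of its purpose. It still leaves everyone but the patient outside the blinding, and no other section brings anyone back in.
- *The endpoints are objective.* This stands for the primary antibody endpoint. It largely stands for cellular responder status too, which is numerical and exploratory.
- *The stratification decision comes before endpoint analysis and rests on baseline counts.* This stands in part. It limits the scope for choosing by result, but does not require those choosing to be masked.
- *Masking of the statistician and the definition of the per-protocol set may be in an analysis plan that is not shown.* This is possible. The absence of a definition is therefore not held against the protocol. The point is that its own blinding statement extends to nobody but the patient.

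A reader might go further and infer that the T-cell laboratory receives the allocation. The documents do not say so. A shared division shows possible access, not actual access.

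A reader might also infer that the stratification can be chosen after the results have been compared by arm. The stated order, counts before any endpoint analysis, does not support that.

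**Conclusion.** The point holds in a limited form, as a cheap improvement. The protocol confines blinding to the patient and shields neither the T-cell laboratory nor the analysts. The consequence is small for measurement of the primary endpoint. It is somewhat larger for the two exploratory IFN-gamma endpoints, and most relevant for decisions on the per-protocol set and the added stratification.

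No numerical size can be given. It is tempting to assume that a few patients per arm are reclassified and to quote an inflated false-positive rate, but the documents give no reclassification rate, no direction and no cellular response rate. Any such figure would only return its own assumptions. For the cellular endpoints it would also describe tests that the protocol declares exploratory and leaves without adjustment for multiple testing.

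The conclusion rests on two assumptions: that no masking is laid down in a document not shown, and that people who know the arm may take part in the decisions listed above, which the protocol permits but does not state.

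**What to change.** Amend section 5 and the Blinding subsection of section 6 to state that:

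- patients are blinded to the vaccine given;
- samples reach both laboratories labelled only with the subject identification number, without the allocation;
- the statistician stays masked to arm until assay validity, the per-protocol set and any update of the analysis plan for stratification are final and documented;
- vaccinating staff are unblinded.

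Add a cross-reference in the closing paragraph of section 8, so that the decision on stratification is taken masked as well as before endpoint analysis.

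The cost is small but not nil. The allocation list must be kept from both laboratories and from the statistician. Safekeeping gives the research team access to the database, so the allocation has to be held apart from what the statistician can see. One documented release step is needed. Sample size, power, visits and patient care do not change.

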### Study population

The study population comprises kidney transplant recipients without detectable SARS-CoV-2 spike protein antibodies at least 4 weeks after the second dose of a mRNA based vaccine.

### Inclusion criteria

- patient has received a kidney transplantation
- full SARS-CoV-2 vaccination with mRNA vaccine (two doses) at least 4 weeks before screening
- > 18 years of age
- no SARS-CoV-2 spike protein antibodies at least 4 weeks after the second dose of an mRNA vaccine

### Exclusion criteria

- acute illness with fever
- Prior documented infection with SARS-CoV-2
- triple anticoagulation therapy
- Subject is currently enrolled in or has not yet completed at least 30 days since ending other investigational device or drug trial(s), or subject is receiving other investigational agent(s)
- Subject has known sensitivity or intolerance to any of the products to be administered for the purpose of this study

- Subject has any kind of disorder that compromises the ability of the subject to give written informed consent and/or to comply with the study procedures
- Subject is pregnant or breast feeding

Females of childbearing potential may participate in this clinical trial, although a negative pregnancy test is required during screening.

## 6. Methodology

### Subject enrollment:

All subjects must personally sign and date the consent form before any screening procedures are performed. Patients are eligible for enrollment when they have satisfied all of the inclusion/exclusion criteria. Following enrollment patients will be randomized to one of the treatment groups. All participants who enter into the screening period for the study (after signing the informed consent) will receive a personal identification number. This number will be used to identify the subject throughout the trial and must be used on all study documentation related to the subject. The subject identification number must remain constant throughout the entire trial.

### Patient screening

Patients followed at the transplant clinic of the Medical University of Vienna who received two doses of mRNA-based SARS-CoV-2 vaccine will be invited to the study. In the screening phase kidney transplant recipients that are followed at the kidney transplant clinic of the Medical University of Vienna that fulfill the mentioned inclusion criteria will be identified.

Following informed consent, patients will be tested for SARS-CoV-2 spike protein and nucleocapsid antibodies. Screening has to be performed within 4 weeks prior to vaccination.

### Randomization

Randomization will be performed as soon as the SARS-CoV-2 antibody status is available.

- Patients included in the study will be randomized 1:1 to receive a third dose of the previously administered mRNA vaccine (mRNA-1273 or BNT162b2) or a single dose of Ad26COVS1
- Randomization will be stratified by the maintenance immunosuppressive regimen calcineurin inhibitor (CNI) vs co-stimulation blockade (Beletaccept)
- To ensure that comparison groups will be of approximately the same size a block randomization will be used in order to balance subjects randomized to each group (<https://www.meduniwien.ac.at/randomizer/>).

### Blinding

Patients will be blinded for the treatment.

### Prohibited medication

The exclusion criteria describe triple anticoagulation as prohibited medication in this trial.

There are no prohibited therapies during the Post-Treatment Follow-up phase

## Treatment

Patients will receive a single dose of the study drug intra muscular (i.m.) within 28 days after screening. Patients will receive a time slot for vaccination following randomization.

Vaccination will be performed at the outpatient clinic of the Division of Nephrology and Dialysis at the Medical University of Vienna (chronic hemodialysis unit and pre-transplant clinic).

## Study medication, Dosage and Administration

Study medication will be provided by the central pharmacy of the Medical University of Vienna.

Treatment arm 1 (“more of the same”):

active substance: mRNA-1273

trade name: COVID-19 Vaccine Moderna

Manufacturer: ROVI PHARMA INDUSTRIAL SERVICES S.A.

Route of administration: i.m.

Duration: once

Dose: 0.5 ml

*or*

active substance: BNT162b2

trade name: COMIRNATY COV-19 VAC

Manufacturer: BIONTECH MANUFACTURING GMBH

Route of administration: i.m.

Duration: once

Dose: 0.3 ml

Treatment arm 2 ("mix and match"):

active substance: Ad26COVS1

trade name: COVID-19 Vaccine Janssen

Manufacturer: JANSSEN BIOLOGICS B.V.

Route of administration: i.m.

Duration: once

Dose: 0.5 ml

#### Study-drug delivery and drug storage conditions

The vaccines are prepared and dispensed by the central pharmacy of the General Hospital of Vienna. All trial substances will be handled and administered according to manufacturer's recommendations.

#### Follow-up:

Follow up visits will be scheduled 4, 8, 12, 24 and 48 weeks after vaccination at the kidney transplant outpatient clinic to assess the immune response to the vaccination (blood draw for antibody and T-cell measurement). Independent from study visits, patients are routinely followed at the transplant clinic of the Nephrology Department of the Medical University of Vienna at regular intervals including blood draws (creatinine, immunosuppression levels).

### Study duration

The response to the vaccination will be evaluated at day 29-42 (visit 3, primary endpoint) as well as day 57-70, day 85-98, day 168-198 and day 336-364 (visit 4, 5, 6 and 7, secondary endpoints).

### End of study

The end of the trial is the last visit of the last patient.

